#### (4) Sample size

Because no previous orthogonally designed study provides a significant difference of MoCA or MMSE scores for rTMS treatment to PSCI, which would allow us to accurately estimate the adequate sample size for this trial, we decided to recruit 45 PSCI patients who will be randomly divided into nine groups and three subgroups based on orthogonal design (5 patients per group, 15 patients per stimulating site subgroup), in consideration of the research grant, the recruitment feasibility and the recommended sample size in neuroimaging research (medians:14.5) [17].

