#### (5) Discontinuing criteria

Patients who simply wishes to stop participation;Patients who could not undergo the baseline assessment;Patients who did not complete the rTMS treatment sessions;Patients who suffered from worsening symptoms.

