### 3. Outcomes

The primary outcomes are the Montreal Cognitive Assessment Beijing Version (MoCA-BJ) and the Trail-Making Test (TMT). The secondary outcomes are the modified Barthel index (MBI), the Lawton Instrumental Activities of Daily Living Scale (LIADL), the stroke-specific quality of life (SS-QOL), the functional magnetic resonance imaging (fMRI) scan and the adverse events. All measurements of clinical assessments were administered three times: pre-treatment (baseline), post-treatment, and at a three-month follow-up. All of the cognitive assessments were performed by a trained neuropsychologist who was blind to the treatment status of the participants throughout the study. The MRI scan were conducted at baseline and at the end of rTMS treatment.

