### 4. Statistical analyses

The data of MoCA-BJ, TMT, MBI, LIADL and SS-QOL were shown as mean ± standard deviation (SD) and analyzed by the range analysis and one-way analysis of variance (ANOVA), which was used the SPSS 22.0 software (IBM, Armonk, NY, USA, 2020). The range analysis was used to determine the influence of each parameter at a specific level on the effect indicator and obtain the optimum combination of rTMS parameters. The one-way ANOVA was used to determine the statistical significance in nine different parameters’ combination of rTMS. P < 0.05 was considered significant.

For ALFF and FC maps, paired T-test will be used for intra-group comparison and one-way ANOVA analysis will be used for inter-group comparison in the three stimulating site subgroups. Then multiple comparison correction will be performed using Gaussian random field theory (GRF) with voxel *p* < 0.005, cluster *p* < 0.05. The Pearson correlation analyses were used to calculate the correlations between the changes in ALFF and FC with the clinical symptom scores at baseline and the end of the rTMS treatment (*p* < 0.05).

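### For the clinical scores, the only planned test pools all four rTMS parameters, and the optimum is picked by a range analysis that has no error term

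*Protocol article*

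**What the plan says.** The Introduction sets the aim as finding the best regimen over four parameters and also hypothesises interactions between them. Section 3 (Outcomes) names MoCA-BJ and TMT as primary.

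Section 4 (Statistical analyses) gives MoCA-BJ, TMT, MBI, LIADL and SS-QOL the same two methods:

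- **Choosing the optimum:** "The range analysis was used to determine the influence of each parameter at a specific level on the effect indicator", and also to obtain the best combination.
- **Significance:** "The one-way ANOVA was used to determine the statistical significance in nine different" parameter combinations, with the rule "P < 0.05 was considered significant".

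No test or interval is attached to an individual parameter for these scores. For the ALFF and FC maps, "one-way ANOVA analysis will be used for inter-group comparison in the three stimulating site subgroups".

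The Sample size section gives "5 patients per group, 15 patients per stimulating site subgroup" and no power figure. On timing, section 3 states: "All measurements of clinical assessments were administered three times: pre-treatment (baseline), post-treatment, and at a three-month follow-up".

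**The concern.** The method that answers the trial's question carries no measure of error, and the method that carries one answers a different question. A significant nine-group ANOVA does not say which parameter or level is responsible. A non-significant one does not stop the range analysis from naming a best combination, because nothing in section 4 makes the choice depend on the test.

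The Abstract says the results should support standardised use of rTMS. A ranking that could be chance would then be read as a recommended regimen. This is an analysis that the article states, not a detail left to a fuller document.

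**Working it through.** **Inputs from the protocol.** Nine groups of 5, so 9 × 5 = 45 patients and 45/3 = 15 per site. Table 2 is orthogonal, so there are also 15 per level of every other parameter. Alpha is 0.05. The protocol gives no effect size, SD, baseline–outcome correlation or power, so there is no power figure to reproduce.

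**Assumptions.** Complete data; equally spaced level means −d/2, 0, +d/2 in SD units; baseline–outcome correlation r = 0.5, 0.6 or 0.7.

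**Step 1: what the ANOVA tests.** Nine groups give 9 − 1 = 8 between-group df. Four parameters at three levels use 4 × 2 = 8 df. The array is saturated, so the nine-group F is one pooled test of all four parameters. The error df are 45 − 9 = 36, so a 2-df test per parameter is available but not planned.

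**Step 2: range analysis when nothing works.** Each level mean has standard error 1/√15 = 0.26 SD. Simulation with no effect gives:

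- expected range for one parameter: 0.44 SD
- largest of the four ranges: mean 0.69 SD, 95th percentile 1.04 SD
- chance that any given combination is named: about 1/3⁴ = 1/81.

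With all four parameters truly at 0.5 or 0.8 SD best-to-worst, the fully correct combination is picked 27% or 54% of the time.

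**Step 3: power.** With one active parameter the noncentrality is λ = 15·d²/2. At d = 1.0, λ = 7.5. With baseline as covariate, λ becomes 7.5/(1 − r²): 10.0, 11.7 and 14.7 for r = 0.5, 0.6 and 0.7. Bonferroni over four parameters uses 0.05/4 = 0.0125.

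| Test, one active parameter, d = 1.0 SD | Power |
|---|---|
| Planned F(8,36), post-treatment score | 37% |
| Planned F(8,36), change score, r = 0.5/0.6/0.7 | 37/46/60% |
| Parameter F(2,36), unadjusted | 65% |
| Parameter F(2,36), Bonferroni | 42% |
| Parameter F(2,35) with baseline, Bonferroni, r = 0.5/0.6/0.7 | 57/66/79% |

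At d = 0.8 SD the planned test has 23%. The Bonferroni parameter test has 24% without baseline, and 35% (r = 0.5) or 54% (r = 0.7) with it.

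With k equally active parameters, λ for the pooled test is k × 7.5. At d = 1.0 its power is about 69% for two and 96% for four.

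**Step 4: multiplicity.** Four unadjusted 5% tests sharing one error term give about an 18% chance of at least one false positive when nothing works.

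**Step 5: interactions.** Suppose a benefit exists only when TPC is combined with 20 Hz. In Table 2 that is group 8 alone, which is one of three groups at 90% RMT and one of three at 2000 pulses. One third of the benefit therefore appears as an advantage of 90% RMT, and one third as an advantage of 2000 pulses, although neither has an effect of its own.

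**Step 6: coding.** Table 2 and the group list below it disagree on intensity and pulse number in six groups.

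| Group | Table 2 | Group list |
|---|---|---|
| 2 | 100%, 1000 | 90%, 1500 |
| 3 | 90%, 1500 | 100%, 1000 |
| 4 | 110%, 1000 | 90%, 2000 |
| 7 | 100%, 2000 | 110%, 1500 |
| 8 | 90%, 2000 | 110%, 1000 |
| 9 | 110%, 1500 | 100%, 2000 |

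Both arrays are orthogonal, so the power figures hold under either, but the parameters cannot be coded until the two are reconciled.

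**The case against.** The best defence is that the pooled ANOVA is a legitimate gatekeeper. It is one test at 5%, assumes no additivity, and gains power as more parameters act. Much of the apparent advantage of parameter tests (65% against 37%) is uncorrected multiplicity: after Bonferroni it is 42% against 37%. Baseline adjustment would also help the pooled test, to 48% at r = 0.5 and 68% at r = 0.7. All of this stands, so the power argument is secondary. None of it lets the pooled test identify a parameter, and section 4 does not use it as a gate.

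The protocol also lists the small sample as a limitation and calls for a larger study. That tempers how the result may be read, but it puts no uncertainty on the named optimum.

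A reader might infer more than the document supports:

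- **That no parameter is ever tested.** Site is tested on the ALFF and FC maps.
- **That baseline scores are ignored.** Section 4 does not say whether the analysed quantity is a post-treatment or a change score, and an article may leave covariates to a fuller plan.
- **That early stoppers leave the analysis and unbalance the array.** The Discontinuing criteria list "Patients who did not complete the rTMS treatment sessions", but do not say that these patients go unassessed or unanalysed.

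**Conclusion.** The point holds for the clinical outcomes, including both primaries. The plan selects a best level of each parameter without any parameter-level inference, and its one test cannot supply that inference. The firmest figure needs no assumed effect: with normal scores, complete data and no true differences, the leading parameter still shows a best-to-worst gap averaging about 0.7 SD.

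It would be too strong to say that the planned ANOVA always wastes power. The loss is real when one parameter acts and baseline correlates well with outcome. It nearly vanishes under Bonferroni without baseline. With several active parameters the pooled test is the more powerful one for detecting that something differs. All power figures rest on assumed effect sizes and correlations.

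Parameter tests have a limit of their own: in a saturated L9 they are valid only if the interactions that the Introduction hypothesises are absent. The range analysis depends on the same condition without saying so. Any optimum from this trial is therefore exploratory.

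**What to change.** 1. For each clinical score, replace the one-way ANOVA with a linear model: score = site + frequency + intensity + pulse number + baseline score. Report a 2-df F-test per parameter.
2. State a multiplicity rule across the four parameters, for example Holm, which is never less powerful than the Bonferroni figures above. It does not cover the two primary outcomes or the two post-baseline visits, so name the visit and outcome to which it applies.
3. Report adjusted level means and level differences with 95% confidence intervals.
4. Call a level optimum only where that parameter's adjusted test supports it. Otherwise state that no level was shown to be better. Keep the range analysis as description.
5. Label the optimum exploratory and state the no-interaction assumption.
6. Reconcile Table 2 with the group list for groups 2, 3, 4, 7, 8 and 9 before the parameters are coded.

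The cost is a rewrite of the statistical section, one SPSS general linear model per outcome, and one df for baseline (36 to 35 error df). It needs no extra patients or visits. The real price is that fewer results will be labelled optimum.

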**Methods:**

A single-center, orthogonally-designed, triple-blind randomized controlled trial will be conducted and forty-five PSCI patients will be recruited and randomly assigned to one of nine active rTMS groups based on four rTMS paraments: stimulating site, frequency, intensity and pulse number. Neuropsychological, activities of daily living, quality of life and functional magnetic resonance imaging (fMRI) evaluations were be performed pre-, post- and 3 months after rTMS.

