## Introduction

Post-stroke cognitive impairment (PSCI) is one of the vascular cognitive impairments and probably develop into dementia [1]. It was reported that 20–70% stroke survivor suffered from the cognitive impairment within 6 months after stroke attack [2, 3]. It is not only a common, important disability after stroke but also could hinder the rehabilitation of stroke-related sequelae including motor dysfunction, sensor deficits and the limited activities of daily living [4]. The pathogenesis of PSCI is multifactorial being similar with VCI. In terms of brain structure, it is generally related to focal, multifocal or diffuse cortical and/or subcortical large infarct, microinfarcts or lacunes, as which is often affected important brain areas (thalamus, frontobasal and/or limbic systems, etc.) [5]. Functionally, the PSCI is due to the disfunction of neuronal metabolism, activation and connectivity, while the exact mechanism between vascular lesion, cognition, and neuroplasticity are not completely understood [6]. Current research shows that many non-invasive neuromodulatory techniques could improve cognitive impairment via neuroplasticity [7]. As a non-invasive brain stimulation,the repetitive transcranial magnetic stimulation (rTMS) was widely used as a primary or an add-on treatment to improve cognitive function in patients with stroke [8]. Several meta-analyses confirmed its promising and positive effect on PSCI [9–11]. In these studies, mostly rTMS schemes included four primary parameters: stimulating site, frequency, intensity and pulse number, however, the rTMS intervention scheme varied substantially and the considerable heterogeneities of rTMS parameters were the great challenging in its clinical practice. Furthermore, although accumulating studies have shown that rTMS could improve the cognitive function in many neurological and psychological diseases [12, 13], the brain functional mechanism is still unclear. The present study hypothesized that rTMS could promote the cognition recovery with an optimal parameter combination and it might be objectively existed that the interaction effects between the four parameters: stimulating site, frequency, intensity and pulse number. Furthermore, we predicted that the mechanism of rTMS might be related with the neuroplasticity in three brain networks: default mode network (DMN), dorsal attention network (DAN), central executive network (CEN). Hence, the prospective, single-center, orthogonally-designed, triple-blind randomized controlled trial will be conducted and will be aimed to explore the rTMS optimum parameters regimen for PSCI based on stimulating site, frequency, intensity and pulse number and the neuroimaging mechanism in default mode network (DMN), dorsal attention network (DAN), central executive network, (CEN) following rTMS treatment in PSCI patients. All participants will be assigned averagely to one of nine paralleled active rTMS groups which are designed according to the L_9_(3^4^) orthogonal array with four different parameters: stimulating site, frequency, intensity and pulse number. This trial protocol will be written in adherence to the standard protocol items: recommendations for interventional trials (SPIRIT) 2013 guidelines [14].

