#### (2) Eligibility criteria

The study researchers will execute the eligibility screen in accordance with the inclusion and exclusion criteria. All the participants should sign an informed consent after eligibility confirmation.

Inclusion criteria:

Male or female patients between 18 and 75 years of age;Right-handed;Patients who meet the diagnostic criteria for vascular cognitive impairment reported in the Guidelines from the Vascular Impairment of Cognition Classification Consensus Study [15] and the Chinese vascular cognitive impairment guideline 2019 [16] as which mainly be concluded as: (1) Cognitive impairment at least one domain in attention and executive, memory, language and visuospatial function confirmed by clinical and neuropsychological evaluation (MoCA ≤ 24) with or without the impairment in instrumental activities of daily life (IADL); (2) Imaging evidence due to stroke confirmed by magnetic resonance imaging (MRI); (3) Cognitive impairment should be independent of the motor/sensory sequelae of the vascular event and with a clear temporal relationship (within 6 months and lasted for at least 3 months) between a vascular event and onset of cognitive deficits;No severe aphasia (Unable to accomplish cognitive tests);Normal cognitive functions before stroke;Voluntary participation and signed the informed consent (Signed by the patient or the authorized person).

Exclusion criteria:

Cognitive impairment due to primary or secondary neurological disease, such as normal cranial pressure hydrocephalus, frontotemporal dementia, Parkinson’s disease, multiple sclerosis, encephalitis and delirium;Cognitive impairment due to depression, schizophrenia, bipolar disorder, psychotic disorder, vitamin D deficiency, toxicosis or else systematic diseases;Drug/alcohol abuse/dependence within the last 3 months of first recognition of impairment.rTMS treatment contraindications such as epilepsy patients, pregnant or lactating women or with a metal or electric implanted device (eg. deep brain stimulator, ventriculoperitoneal shunt, aneurysm clip, pacemaker, cochlear, surgical staples on the scalp).MRI contraindications (such as metal implants or claustrophobia)participating in a concurrent pharmacological or nonpharmacologic treatment research.

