#### (6) ALFF and FC

The amplitude of low frequency fluctuation (ALFF) and functional connectivity (FC) will be used to explore different brain effects in the three stimulating -site subgroups.

The ALFF refers to the low frequency fluctuation of BOLD signal of the brain voxel, which will be calculated with DPARSF package after data preprocessing. The generated ALFF maps will be used for statistical analysis.

FC will be used to explore the functional connectivity changes in three brain networks (default mode network, DMN; dorsal attention network, DAN; central executive network, CEN) after treatment, which were obtained by meta-analysis (http://www.neurosynth.org/), were used as imaging indicators to analyze according to the methods described by Tomasi et al. [32]. First, Independent component analysis (ICA) will be used to extract DMN, DAN and CEN networks of the three groups, and then the brain regions with differences in the corresponding network will be found by visual observation, which will be used as regions of interest (ROI) to conduct Pearson correlation with the whole brain voxel. The FC maps obtained will be used for statistical analysis.

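### With all nine groups on active rTMS, the within-site paired tests on ALFF and FC and the imaging-clinical correlations cannot show what rTMS itself does to the brain networks

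*Protocol article*

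**What the plan says.** **Allocation.** The abstract states that patients are "randomly assigned to one of nine active rTMS groups based on four rTMS paraments". The Participant timeline, Randomization and blinding, and rTMS protocol sections agree. No sham, untreated or usual-care group is described, although the trial is labelled a randomised controlled trial.

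**Hypotheses (Introduction).** On efficacy: "The present study hypothesized that rTMS could promote the cognition recovery with an optimal parameter combination". On mechanism: "we predicted that the mechanism of rTMS might be related with the neuroplasticity in three brain networks", namely the DMN, DAN and CEN. The Discussion asks whether activity and connectivity in these networks are enhanced, and related to cognitive improvement, after rTMS.

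**Imaging analysis.** Section 3(6), ALFF and FC, states that "FC will be used to explore the functional connectivity changes in three brain networks" after treatment. Section 4 states that "paired T-test will be used for intra-group comparison and one-way ANOVA analysis will be used for inter-group comparison in the three stimulating site subgroups", with Gaussian random field correction at voxel p < 0.005 and cluster p < 0.05. It also plans Pearson correlations of ALFF and FC change with clinical scores. It does not say whether the ANOVA uses change maps or post-treatment maps, and it does not call any of these tests descriptive.

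**Clinical analysis.** Section 4 analyses MoCA-BJ, TMT, MBI, LIADL and SS-QOL by range analysis and one-way ANOVA across the nine combinations. No paired test is planned for them.

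**Limitations.** The closing paragraph of the Discussion names sample size, single centre, simple parameter levels and heterogeneous oral medication. It does not name the absence of an unstimulated control.

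**The concern.** A paired test asks whether the mean change in a subgroup differs from zero. To attribute that change to rTMS, one must assume that it would have been zero without rTMS. Nothing in the design supplies or checks that assumption, and the protocol itself gives reasons to doubt it:

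- The entry criterion on timing reads "with a clear temporal relationship (within 6 months and lasted for at least 3 months"). It sets no upper limit on time since stroke, so some patients may still be changing.
- Section 2(4) permits individualised routine medical care during the trial. It prohibits cognition-improving drugs, which removes one competing cause but not the others.
- The two scans lie about five weeks apart (W0 and W5), so ordinary scan-rescan change enters every paired map.

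The correlations have the same weakness. Spontaneous recovery could move imaging and clinical scores together, and a correlation between them would then appear with no rTMS effect.

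At stake is the trial's second stated aim. A positive within-site map could be presented as rTMS-induced neuroplasticity when the design cannot identify its cause.

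**Working it through.** **1. The protocol's own figures.** Section 1(4) gives 5 patients per group and 15 per site subgroup. 9 × 5 = 45, and 45 / 3 = 15. Both reproduce. The section states no power, effect size or SD, so there is nothing further to reproduce.

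**2. What each planned analysis can identify.**

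| Analysis (section 4) | Comparison | Protected by randomisation? |
|---|---|---|
| Clinical range analysis and ANOVA | Between combinations | Yes; a shared drift cancels |
| ALFF/FC one-way ANOVA | Between site subgroups | Yes; a shared drift cancels |
| ALFF/FC paired t-test | Post versus pre within a site | No |
| Imaging-clinical correlations | Association across patients | No |

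Write a patient's change as *background drift + rTMS effect at that site + error*. The paired test estimates drift plus effect. The difference between two sites estimates only the difference between their effects, because randomisation gives both sites the same expected drift.

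**3. Illustration of size.** Inputs:
- n = 15 per site subgroup (section 1(4))
- voxel threshold 0.005 (section 4), taken as two-sided, which is an assumption
- true rTMS effect of zero
- drift of *d* SDs of the change score. **The documents give no value for *d*; 0.3 to 0.7 is an assumed range.**

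Under these inputs the paired t statistic follows a noncentral t distribution with 14 degrees of freedom and noncentrality d√15. The two-sided critical value at 0.005 is 3.326. The rejection probability is P(|T| > 3.326).

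| Assumed d | d√15 | Paired test passes p < 0.005, per voxel |
|---|---|---|
| 0 | 0 | 0.5% |
| 0.3 | 1.162 | 3.6% |
| 0.5 | 1.936 | 12.9% |
| 0.7 | 2.711 | 32.0% |

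These are per-voxel figures before the cluster step. They are not the false-positive rate of the whole map.

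**4. The contrast that randomisation protects.** With three subgroups of 15, no rTMS effect and a shared drift, 20,000 simulated trials per setting gave these rejection rates at 0.05 for a one-way ANOVA on change: 5.0% (d = 0), 5.1% (d = 0.2), 5.0% (d = 0.5) and 4.8% (d = 0.8). Shared drift leaves this test at its nominal level.

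**5. Why the correction does not help.** Random field correction limits chance findings over many voxels when the true mean change is zero. If background processes make the true mean change non-zero, the paired test detects a real change. The error lies in naming rTMS as its cause, and no threshold corrects that.

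**The case against.** **The main question is comparative and needs no sham arm.** This stands. The chief aim is to find the optimum parameters, the efficacy hypothesis is tied to an optimal combination, and all clinical outcomes are compared between combinations. A reader might infer that the missing control undermines the parameter ranking. The protocol does not support that, because a shared drift cancels there.

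**No paired test of MoCA or TMT is planned.** This stands too. A reader might infer that pre-post cognitive gains will be tested and credited to rTMS. Section 4 reserves paired tests for the ALFF and FC maps. Regression to the mean after selection on MoCA ≤ 24, and practice on repeated tests, act on cognitive scores; they reach the imaging conclusions at most through the correlations.

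**The imaging is secondary and exploratory, and the between-site ANOVA is already planned.** This is true and lowers the severity. It does not remove the problem: the network mechanism is a stated aim, the paired tests carry no caveat, and the ANOVA is not designated as the basis for the mechanism conclusion.

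**The illustration rests on an assumed drift and ignores the cluster step.** Correct. It shows the direction and how sensitive the test is, and does not estimate this trial's error rate. Figures for one paired test at p < 0.05 would be larger still but match no planned analysis, so they are not used.

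**A deficit lasting at least 3 months partly guards against early recovery.** Partly, yes. It does not show that change without rTMS is zero.

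**Conclusion.** The concern holds for the within-site paired tests on ALFF and FC, for the imaging-clinical correlations, and for any statement that rTMS as such promotes recovery or alters the DMN, DAN or CEN. It does not extend to the clinical range analysis and ANOVA across combinations, or to the between-site imaging ANOVA.

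The logical point needs only the facts that all groups are active and that the tests are within-group. The size depends on a drift that the documents do not give: for an assumed 0.3 to 0.7 SD, about 4% to 32% per voxel against 0.5% nominal, before the cluster step.

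Two further inferences are not supported. Section 2(4) permits routine medical care and does not name rehabilitation, so concurrent rehabilitation cannot be cited from it as a competing cause. Adjusting for time since stroke would not replace the missing control, since the between-level contrasts are already randomised. That the paired results will be misattributed is an inference from the hypotheses and the absence of a caveat; no sentence rests the mechanism conclusion on the paired tests alone.

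Severity: should be fixed. It concerns how a secondary analysis is interpreted, but it changes what the trial may validly conclude on its second aim.

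**What to change.** 1. **Section 4.** State that the between-site one-way ANOVA is run on post-minus-pre ALFF and FC maps and is the inferential test for site-specific network effects.
2. **Section 4.** Label the within-site paired tests and the imaging-clinical correlations as descriptive and not attributable to rTMS.
3. **Introduction and Discussion.** Word the hypotheses comparatively: which levels of site, frequency, intensity and pulse number give the larger change, and whether network change differs between sites. Add the absence of a sham or untreated control to the limitations.

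The cost is wording and one clarified input to an analysis already planned, with no new patients, scans or procedures. The downside is a narrower mechanism claim: the trial could report that network change differs between sites, but not that rTMS causes it. If all sites had the same effect, the ANOVA could not detect it.

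### The between-site imaging ANOVA does not name the scan or contrast it compares and makes no stated use of the baseline scan; a baseline-adjusted ANCOVA would be clearer and more precise

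*Protocol article*

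**What the plan says.** All references are to the Protocol article.

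- **Tests.** Section 4 (Statistical analyses) provides that, for the ALFF and FC maps, a "paired T-test will be used for intra-group comparison and one-way ANOVA analysis will be used for inter-group comparison in the three stimulating site subgroups". It gives no dependent scan, difference map, baseline covariate or time factor for the ANOVA.
- **Data that enter.** Section 3, item (6) ALFF and FC, says only "The generated ALFF maps will be used for statistical analysis" and "The FC maps obtained will be used for statistical analysis".
- **Aim.** The same item states that "FC will be used to explore the functional connectivity changes in three brain networks" after treatment, and that ALFF and FC are to show how brain effects differ between the three site subgroups.
- **Scans available.** Section 3 (Outcomes) states "The MRI scan were conducted at baseline and at the end of rTMS treatment". The participant timeline lists fMRI at W17 as well as at W0 and W5.
- **Where change is named.** In the section 4 imaging paragraph the word occurs only for the "correlations between the changes in ALFF and FC with the clinical symptom scores".

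**The concern.** The between-site ANOVA is the only comparison between randomised groups in the imaging part. Three separate paired t-tests, one per site, cannot show that sites differ in response: significance at one site and not at another is not a test of the difference. The claim that brain effects depend on site therefore rests on the ANOVA.

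A one-way ANOVA with site as its only factor has no place for the baseline scan unless that scan is built into the dependent map, and the text does not say that it is. Three readings are open: W5 maps, W5 minus W0 difference maps, or maps from baseline or from both scans pooled. They differ in precision, and the last would not answer the stated question. The number of patients was set by grant, feasibility and a median from imaging research, so it cannot easily be raised. The baseline scans already planned are the cheapest source of extra precision.

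**Working it through.** **Inputs from the document.** Nine groups of 5 give 9 × 5 = 45 patients, and three sites of 15 give 3 × 15 = 45, so the stated sample size is consistent. The plan gives no power figure to reproduce. The imaging threshold is voxel p < 0.005 with cluster p < 0.05 under Gaussian random field (GRF) correction.

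**Assumptions not in the document.** A site effect of f = 0.40 in units of the W5 between-patient SD; equal SDs at both scans; baseline-to-W5 correlation r from 0.2 to 0.8. Each calculation is for a single voxel or summary value and ignores the cluster step.

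**Step 1: residual variance, with W5 variance set to 1.**
- W5 map alone: 1
- Difference map: 2(1 − r)
- ANCOVA on the baseline map: 1 − r²

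At r = 0.4, 0.6 and 0.8 the ANCOVA variance is 0.84, 0.64 and 0.36. This is worth 1/0.84 = 1.19, 1/0.64 = 1.56 and 1/0.36 = 2.78 times as many patients analysed on W5 maps alone.

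**Step 2: power from the noncentral F distribution.** The noncentrality is 45 × 0.40² = 7.2, divided by the residual variance. Degrees of freedom are 2 and 42, or 2 and 41 for ANCOVA.

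| r | W5 alone, 5% | Difference map, 5% | ANCOVA, 5% | W5 alone, 0.5% | ANCOVA, 0.5% |
|---|---|---|---|---|---|
| 0.4 | 63.5% | 55.2% | 71.5% | 28.8% | 36.6% |
| 0.6 | 63.5% | 73.8% | 83.3% | 28.8% | 51.8% |
| 0.8 | 63.5% | 96.4% | 97.8% | 28.8% | 85.7% |

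The difference map equals W5 alone where 2(1 − r) = 1, that is r = 0.5, and is worse below that. At r = 0.2, ANCOVA gives 65.3% against 63.5% at the 5% level, which is no practical gain but no loss.

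**Step 3: is an ANOVA on W5 maps valid?** In 20,000 simulated randomised trials with 15 per site and no site effect, it rejected in 4.9% of trials at r = 0.3 and 4.8% at r = 0.7. With a true difference of 1.00 SD for one site, the mean estimate was 1.00. It is therefore valid and unbiased.

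**Step 4: chance imbalance.** The difference between two site means at baseline has SD √(2/15) = 0.37 of the between-patient SD. The largest and smallest of the three means differ by more than 0.5 SD with probability 36%. On average a fraction r of such a gap carries to W5: for 0.5 SD, 0.4 × 0.5 = 0.2 SD up to 0.8 × 0.5 = 0.4 SD. In simulations without any effect, restricted to trials with a baseline gap above 0.5 SD, the W5-only ANOVA rejected in 7.3%, 9.6% and 12.2% at r = 0.4, 0.6 and 0.8. The overall rate stays near 5%, so false positives gather where baseline was unbalanced. ANCOVA removes this dependence.

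**The case against.** **Randomisation already protects the test.** A reader might infer that an ANOVA on maps cannot test whether response differs by site. For W5 maps that is wrong. Site is a randomised factor, so expected baseline maps are equal, and step 3 shows correct error and no bias. The 36% is the chance of a baseline gap, not a false-positive rate. This objection stands in full against any claim of invalidity. It does not answer the loss of precision.

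**The text does not exclude change.** The reference to maps covers both the paired t-test and the ANOVA, and a paired t-test is itself an analysis of change. Naming change for the correlations does not show that it was excluded elsewhere. Difference maps would fit the stated aim, and a condensed article may leave the contrast to a fuller document. It is fair that the documents do not support saying that change is left out, or that baseline or pooled maps will be used. What remains is that the article chooses a one-factor test and names its input only as maps, so the wording does not fix a test of the stated aim.

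**Change scores may do worse.** A reader might also infer that power is lost relative to change from baseline. That is true only if r exceeds 0.5, and the document gives no r. The gain claimed here is therefore for ANCOVA, which was no worse at any correlation tried.

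**It is a secondary, exploratory outcome.** This is true and limits the weight of the point, but not the case for a correction that needs no new data.

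**Conclusion.** The point holds as one of specification and precision, not of validity. The between-site ANOVA names neither its scan nor its contrast and makes no stated use of the baseline scan. On W5 maps it is a sound but less precise test; on baseline or pooled maps it would not address response, though nothing in the text says that these are intended.

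The gain from ANCOVA over W5 maps at the 5% level is about 8, 20 and 34 percentage points of power at r = 0.4, 0.6 and 0.8 (71.5, 83.3 and 97.8 less 63.5). At the planned voxel threshold, taken as a single test, it is about 8, 23 and 57 points. These sizes rest on the assumed f = 0.40, equal SDs and the assumed r. At r = 0.2 the gain is negligible. The change should be made, but it concerns a secondary outcome and does not threaten the trial.

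**What to change.** In section 4, replace the between-site one-way ANOVA on maps by a voxelwise ANCOVA: W5 map as the dependent variable, site as the factor, and the patient's own W0 map as a voxelwise covariate, for ALFF and FC alike. Keep the GRF correction and its thresholds as planned. The within-site paired t-tests may stay as description.

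If the software cannot take a voxelwise covariate, run the one-way ANOVA on W5 minus W0 difference maps and say so. This is second best, because at r below 0.5 it is less efficient than W5 maps alone.

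The cost is one sentence of wording, no new data and one residual degree of freedom (41 instead of 42).
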